#### Inclusion criteria

Patients with mCRC for whom a cetuximab-based regimen is planned as first-line treatment after considering routine clinical practice, the locally approved label, and the best scientific knowledge. The choice of the chemotherapy regimen for first-line treatment is also at the sole discretion of the investigator, based upon routine clinical practice.Patients aged 20 years and above.Patients pathologically and molecularly diagnosed with wild-type *RAS* CRC.Patients willing to provide blood samples during the study.Patients willing and able to provide signed informed consent.

#### Exclusion criteria

Patients with a history of any anti-EGFR therapy.Contraindications to cetuximab as per the locally approved label.

### Blood sampling

Blood will be obtained from an arterial or venous line according to standard phlebotomy technique, with a Cell Free DNA collection tube (Roche) used for sampling. Blood specimens will be shipped at room temperature within 24 h, and plasma preparation and cfDNA extraction will be performed within 7 days of sampling at Taipei Institute of Pathology.

### *RAS* mutation analysis of cfDNA and tissue samples

Before mutation analysis, cfDNA will be extracted using the Cobas cfDNA sample preparation kit, and a representative tumor sample (primary or metastasis) will be made available for a repeat *RAS* mutation analysis in case of any discordance between the tumor tissue and cfDNA analyses. Three to five sections of a formalin-fixed paraffin-embedded (FFPE) tissue for DNA extraction will be made using the QIAamp DNA FFPE tissue kit. Mutations will be detected using a MassARRAY platform combined with the single allele base extension reaction (SABER) technique (Agena, San Diego, California, USA). In a SABER reaction using the iPLEX enzyme, SABER terminator mix, and extension primer mix (iPLEX Pro kit, Agena), clinically relevant mutations in *KRAS, NRAS* and *BRAF* genes are targeted (Additional file 1: Table S1). After the addition of a cation exchange resin to remove residual salt from the reactions, a purified primer extension reaction is loaded onto the matrix pad of a SpectroCHIP bioarray (Sequenom) by using a MassARRAY nano-dispenser and assayed on the MassARRAY platform. The mutation peaks are identified as a higher than background intensity compared with a non-mutation sample pool.

### Schedule of assessments

Patients will undergo *RAS* mutation analysis of cfDNA every 3 months during cetuximab-based first-line treatment and within 3 weeks of disease progression after first- and second-line treatments. During the study period, the assessment of patients will be scheduled according to the clinical judgment of the responsible investigator. The tumor response will likewise be assessed from the imaging scan at the investigator’s judgment.

### Sample size calculation

The present study aims to identify the frequency of *RAS* mutations in cfDNA during cetuximab treatment. In earlier studies, 21 and 33% of patients with *RAS* wild-type CRC at baseline displayed *KRAS* mutations at week 24 and 26, respectively [13–15]. Sample size is based on test power considerations by using a confidence limit. When the Wilson score method was used, a sample size of 110 produced two-sided 95% confidence intervals (CIs) of 0.169, 0.176, and 0.180 when the sample proportion was 0.300, 0.350, and 0.400, respectively [25]. Taking a 10% dropout rate into account, 120 patients should be enrolled in this study.

### Statistical analysis

The National Health Research Institutes is responsible for data management and statistical analysis. In general, descriptive statistics are used in this study. All patients receiving at least 8 weeks of treatment and having at least one post-baseline *RAS* mutation in their cfDNA will be eligible for clinical efficacy and outcome evaluation (efficacy population). The frequency of *RAS* mutations will be calculated and presented as a number, percentage, and 95% CI for the efficacy population. Clinical responses to cetuximab treatment will likewise be presented as a frequency, percentage, and 95% CI. Cox proportional hazard models will be used to investigate the effect of *RAS* mutations on time-to-event endpoints, including progression-free survival (PFS) and overall survival (OS). Other major clinical variables will also be included in these Cox models (e.g., disease characteristics or type of chemotherapy). Kaplan–Meier survival curves will be produced for PFS and OS of patients with and without genetic mutations. Kaplan–Meier methods will also be applied to the onset time of newly detected *RAS* mutations in cfDNA. The onset time of *RAS* mutations will be censored in patients without mutations at the last available measurement of cfDNA.

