## Methods/design

### Study design

This single-arm, non-interventional, uncontrolled, multicenter study will evaluate the emergence of *RAS* mutations in patients with mCRC receiving a cetuximab-based regimen as first-line treatment. In this investigator-initiated study, patients diagnosed with *RAS* wild-type mCRC will be recruited. Patients for whom treatment is planned with a cetuximab-based regimen under the locally approved label will be enrolled. In addition to cetuximab, infusional 5-fluorouracil is required and combination with oxaliplatin or irinotecan is allowed in first-line treatment. On the basis of the best scientific knowledge, clinical practice for each patient is determined entirely by the responsible investigator. This cetuximab-based treatment is expected to continue until disease progression, intolerable toxic effects, or withdrawal of consent. Blood samples from patients enrolled in this study will be collected before the start of cetuximab-based chemotherapy and then every 3 months during first-line treatment. Blood sampling is also required within 3 weeks of disease progression following cetuximab and second-line treatments. The blood samples will be sent to the central laboratory at Taipei Institute of Pathology and evaluated for the *RAS* genotype by using the MassARRAY technique. Pretreatment tissue sections will also be re-evaluated for the *RAS* genotype by using this technique if a discordance of *RAS* genotype occurs between the tissue and blood samples of the same patient. This study is briefly outlined in Fig. 1.

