### Study objectives

The primary endpoint is the percentage of *RAS* mutations detected in the cfDNA of patients with mCRC during first-line cetuximab treatment. The secondary objectives are the following endpoints: 1. duration between the start of cetuximab treatment and the new detection of a *RAS* mutation; 2. percentage of mutated alleles detected at disease progression; 3. clinical responses and metastasis resection rates during first-line cetuximab treatment; 4. progression-free and overall survival of patients receiving first-line cetuximab treatment; 5. correlations between *RAS* resistance mutations after cetuximab treatment (occurrence and levels) and clinical survival outcomes; 6. total cetuximab dosage in first-line treatment; and 7. correlations between irinotecan or oxaliplatin dosage and acquired resistance to cetuximab.

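### Response, PFS and OS are limited to patients with at least 8 weeks of treatment, although the objectives set them for all patients receiving first-line cetuximab

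*Protocol article*

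**What the plan says.** The Statistical analysis section of the protocol article defines one analysis set. It takes in "All patients receiving at least 8 weeks of treatment" and adds a second requirement in the same sentence: "having at least one post-baseline *RAS* mutation in their cfDNA will be eligible for clinical efficacy and outcome evaluation (efficacy population"). No other population is named for any clinical endpoint. The RAS mutation frequency, which is the primary endpoint, is calculated in this set. The section then states: "Clinical responses to cetuximab treatment will likewise be presented as a frequency, percentage, and 95% CI". It also plans Cox models for PFS and OS, and says that Kaplan–Meier "survival curves will be produced for PFS and OS of patients with and without genetic mutations".

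Study objectives lists the clinical endpoints with no minimum treatment time: "clinical responses and metastasis resection rates during first-line cetuximab treatment" and "progression-free and overall survival of patients receiving first-line cetuximab treatment".

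Study design explains why treatment ends: "This cetuximab-based treatment is expected to continue until disease progression, intolerable toxic effects, or withdrawal of consent". It also requires a blood sample within 3 weeks of progression.

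**The concern.** Completing 8 weeks of treatment is known only after baseline. Since treatment ends at progression or intolerable toxicity, a patient with less than 8 weeks has usually progressed, died, stopped for toxicity or withdrawn. The first three are failures of the treatment course that the clinical endpoints are meant to describe. A patient who has had 8 weeks of treatment was alive at that point and almost always progression-free. If PFS and OS run from treatment start, the curves therefore open with a nearly event-free stretch created by the selection rule. Response and resection rates lose early failures from the denominator.

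The reported figures would then describe patients who tolerated and held on to treatment, not the patients named in the objectives. The primary endpoint is affected too: a patient who progresses at week 6 has a required post-baseline sample but falls outside the set in which the mutation frequency is calculated.

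**Working it through.** **The plan's own figure.** Sample size calculation states that "a sample size of 110 produced two-sided 95% confidence intervals (CIs) of 0.169, 0.176, and 0.180 when the sample proportion was 0.300, 0.350, and 0.400". These figures are interval widths. The Wilson width is 2z/(1+z²/n) × √(p(1−p)/n + z²/(4n²)). With z = 1.96 and n = 110 it gives 0.1689, 0.1755 and 0.1801, which agrees. The article gives no figure for the effect of the 8-week rule, nor any early-stop rate, response rate or median PFS. All such inputs below are assumptions.

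**Share excluded and shift in median PFS, 8-week condition alone.** Eight weeks is w = 1.84 months. Under exponential PFS with median m, and taking everyone who progresses or dies before w as excluded:

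- Share excluded = 1 − 2^(−w/m). This is 13.2% for m = 9, 12.0% for m = 10 and 9.3% for m = 13.
- With time counted from treatment start, the median among those retained is m + w. For m = 10 it is 11.84 months, a rise of 1.84.
- For m = 10, PFS at 6 months moves from 2^(−6/10) = 66.0% to 2^(−(6−1.84)/10) = 74.9%.
- If time were counted from week 8 instead, the exponential model would return a median of m and the shift would vanish. The time origin therefore matters.

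**Response rate, 8-week condition alone.** If a fraction e stops early and none of them responds, a rate r is reported as r/(1−e). For r = 60%:

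| Early stops e | Reported rate |
|---|---|
| 5% | 63.2% |
| 10% | 66.7% |
| 15% | 70.6% |
| 20% | 75.0% |

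**Effect on precision.** Exclusions of 9.3 to 13.2% are 11 to 16 of 120 patients, against the 10 that separate 120 from 110. The loss of precision is small: at n = 104 and p = 0.30 the Wilson width is 0.174 instead of 0.169. The problem is bias, not sample size.

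**Second condition read literally.** Let a fraction π of patients carry a mutation with PFS hazard ratio h, treated for simplicity as a fixed attribute. Solve (1−π)e^(−10λ) + πe^(−10hλ) = 0.5 for λ, so that the median in all patients is 10 months. The median among mutated patients with at least 8 weeks of treatment is ln2/(hλ) + 1.84:

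| h | 8-week rule only | Both conditions, π = 30% | Both conditions, π = 40% |
|---|---|---|---|
| 1 | 11.8 | 11.8 | 11.8 |
| 1.5 | 11.9 | 9.4 | 9.7 |
| 2 | 12.0 | 8.1 | 8.5 |
| 3 | 12.3 | 6.6 | 7.2 |

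So with h of 1.5 or more, the literal set understates the 10-month median. It would also hold only about 36 to 48 of 120 patients before the 8-week rule is applied (120 × 0.30 and 120 × 0.40), and would make the primary mutation frequency 100% by construction. It leaves no one for the curve of patients without mutations and no one to censor in the onset-time analysis. The workable reading is a post-baseline mutation result, but the text does not say that.

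**The case against.** A reader might infer that the rule overstates every clinical outcome. The article does not support that, for three reasons. First, the second condition in the same sentence, taken literally, selects patients with resistance mutations and can pull PFS and OS down. Second, the direction of any bias in the Cox mutation effect cannot be determined. Third, no time origin is stated for PFS or OS; treatment start is named only for the time to a newly detected mutation. The upward direction holds for absolute rates and survival under the 8-week condition alone, with time from treatment start.

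Other points against also carry weight:

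- The magnitudes rest wholly on assumptions. Imaging is at the investigator's judgment, so recorded progression before week 8 may be rarer than an exponential model implies. Counting every early stop as a non-responder is the extreme case.
- The study concerns acquired resistance, and the Discussion cites a report of KRAS mutations generally appearing 5 to 6 months after anti-EGFR therapy. A minimum exposure is a defensible choice for the mutation frequency. It does not carry over to response, PFS and OS.
- The study is single-arm and mainly descriptive, and the clinical endpoints are secondary. That limits the consequences but does not reconcile the analysis set with the objectives.
- Simply restoring early deaths and stops would place patients with little chance of a post-baseline sample in the group without mutations. This would distort the survival comparison, so the fix has to deal with it.

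A fuller analysis plan might define an all-treated population. The rule stated here would still conflict with the stated objectives.

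**Conclusion.** The point holds in limited form. The only stated set for clinical outcomes is selected on a post-baseline condition tied to progression, death and toxicity, and it does not match the population in Study objectives. Alone, the 8-week condition biases absolute response, resection, PFS and OS upward when time runs from treatment start. The illustrative size is 9 to 13% of patients excluded and up to about 1.8 months on median PFS (exponential, assumed median 9 to 13 months), and 60% response reported as 63 to 75% (assumed 5 to 20% early stops, all non-responders). The net direction with both conditions applied as written is not fixed, and nothing firm can be said about the mutation hazard ratio. The rule should be corrected before analysis; it does not call the design into question.

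**What to change.** - Report response, resection, PFS and OS in all enrolled patients who received at least one cetuximab dose. Count early stoppers without a response as non-responders, and state the time origin for PFS and OS.
- Report the mutation frequency in all patients with an evaluable post-baseline cfDNA result, including samples taken at early progression. Reword the second condition to match, so that it agrees with the planned comparison of patients with and without mutations.
- Keep the 8-week set only as a labelled sensitivity analysis.
- For PFS and OS by mutation status, use a landmark analysis with time counted from the landmark, or enter mutation as a time-dependent covariate.

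The cost is a change of analysis-set wording and a little more analysis work, with no new patients, samples or visits. Reported rates and medians will probably be slightly less favourable than under the 8-week rule.

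### The efficacy population admits only patients with a post-baseline RAS mutation, so the primary percentage is about 100% by construction and no mutation-free comparison group remains

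*Protocol article*

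**What the plan says.** The Study objectives section sets the primary measure: "The primary endpoint is the percentage of *RAS* mutations detected in the cfDNA of patients with mCRC during first-line cetuximab treatment".

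The Statistical analysis section defines one analysis set, the efficacy population, by two conditions. The first is duration: "All patients receiving at least 8 weeks of treatment". The second is a mutation: patients "having at least one post-baseline *RAS* mutation in their cfDNA will be eligible for clinical efficacy and outcome evaluation". The next sentence ties the primary result to this set: "The frequency of *RAS* mutations will be calculated and presented as a number, percentage, and 95% CI for the efficacy population".

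The same section then relies on patients who have no mutation. It plans a Cox model for the effect of RAS mutation on PFS and OS, and it states that "Kaplan–Meier survival curves will be produced for PFS and OS of patients with and without genetic mutations". For the time to a newly detected mutation, it censors mutation-free patients at their last cfDNA measurement.

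The Sample size calculation section states that "a sample size of 110 produced two-sided 95% confidence intervals (CIs) of 0.169, 0.176, and 0.180" for sample proportions of 0.300, 0.350 and 0.400. Nothing else in the article redefines the efficacy population.

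**The concern.** A proportion needs a denominator that contains both patients who had the event and patients who did not. Here a patient enters the denominator only by having the event, so the result carries almost no information on how often RAS mutations emerge, which is the study's main question.

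The damage extends to the secondary objectives. Outcome evaluation is assigned to this population, so response, PFS and OS would describe only patients who developed a mutation. In the Cox model, ever having a post-baseline RAS mutation would be a covariate with a single value, and its effect could not be estimated. The mutation-free Kaplan–Meier curve would be empty.

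An analyst would have to follow the rule and report a meaningless primary result, or depart from the published plan. In the second case the denominator could be chosen after the data are seen.

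**Working it through.** **Inputs.** From Sample size calculation: n = 110 evaluable, two-sided 95% Wilson interval, proportions 0.300, 0.350 and 0.400, and earlier-study rates of 21% and 33%. From Statistical analysis: the efficacy population as printed. z = 1.96, z² = 3.84.

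**Step 1: reproduce the plan's figures.** The full width of the Wilson interval is

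2z·√[p(1−p)/n + z²/(4n²)] / (1 + z²/n).

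At n = 110, z²/n = 0.0349 and z²/(4n²) = 0.0000794.

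- p = 0.30: 3.92 × √(0.001909 + 0.000079) / 1.0349 = 0.1689
- p = 0.35: 3.92 × √(0.002068 + 0.000079) / 1.0349 = 0.1755
- p = 0.40: 3.92 × √(0.002182 + 0.000079) / 1.0349 = 0.1801

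These match the stated 0.169, 0.176 and 0.180. The sizing therefore takes all 110 evaluable patients, positive and negative, as the denominator.

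**Step 2: apply the printed definition.** Only positive patients enter, so the set has m = 110p patients and the observed proportion is m/m. For x = n the Wilson lower limit reduces to m/(m + z²).

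| Proportion | Set as printed (m) | Estimate | Wilson 95% CI as printed | Wilson 95% CI with all 110 | Mutation-free patients excluded |
|---|---|---|---|---|---|
| 0.30 | 33 | 100% | 33/36.84 = 0.896 to 1.000 | 0.222 to 0.391 | 77 |
| 0.35 | 38 (38.5 before rounding) | 100% | 38/41.84 = 0.908 to 1.000 | 0.267 to 0.443 | 72 |
| 0.40 | 44 | 100% | 44/47.84 = 0.920 to 1.000 | 0.313 to 0.493 | 66 |

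At the earlier-study rates of 21% and 33%, about 23 and 36 patients remain, with lower limits 23/26.84 = 0.857 and 36/39.84 = 0.904. The estimate is again 100%. The underlying rate changes the size of the set but not the reported percentage.

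**Step 3: how far below 100% could it fall?** The entry condition says post-baseline, while the primary endpoint is limited to first-line cetuximab treatment. A patient first positive outside the counted window could enter the set and still count as negative. Let F be the number positive within the window and L the number positive only later. The reported percentage is F/(F + L). It equals the intended F/110 only if L = 110 − F, that is 77 patients at 30% or 66 at 40%. Every one of the 110 would then have to become positive at some time. In all other cases the percentage is too high. Any comparison by mutation status would also set earlier-detected against later-detected mutations, not mutated against mutation-free patients.

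**The case against.** The strongest reply is that a word was dropped and an assessment, not a mutation, was meant. The sizing, the curves by mutation status and the censoring rule all need mutation-negative patients, so a reader can recover the intent. Blood is collected from all enrolled patients, so no data are lost. A journal article also condenses a fuller protocol, and the slip may exist only here. That reading is likely right. It explains the error but does not correct it: the phrase is the only stated rule for the primary denominator, and the conflicting sentences do not replace it.

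Three narrower points stand as qualifications.

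- The 100% is the literal-reading limit. Samples are also taken at progression after first-line and second-line treatment. The abstract lists the progression sample separately from those taken during treatment, so it is unclear whether a mutation first seen at first-line progression counts. Patients positive only in such samples could pull the figure below 100%, as Step 3 shows.
- The 0.30–0.40 values are proportions chosen for a precision calculation, not a firm forecast. Table 1 of the article spans 13–60%, so a mutation-free majority is likely but not certain.
- The Cox and Kaplan–Meier sentences name no population. Outcome evaluation is nevertheless assigned to the efficacy population, and no other set is defined.

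**Conclusion.** The concern holds and must be fixed. As printed, the efficacy population is selected on the primary outcome. With about 110 evaluable patients and a mutation proportion of 30–40%, it would hold 33–44 patients and give an estimate of about 100% (lower limits 0.896 to 0.920). The planned result was 30–40% with an interval width of 0.169–0.180. The 66–77 mutation-free patients needed for the survival comparisons would be excluded.

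These counts assume a literal reading, 110 evaluable patients, and mutations detected within the window that counts for the primary endpoint. Relaxing the last assumption lowers the percentage, but it remains conditional on having a mutation and does not estimate the planned quantity. The sample-size widths themselves are correct; the fault is in the population definition.

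**What to change.** Replace the second entry condition with at least one evaluable post-baseline cfDNA RAS result, whether mutant or wild-type. State that this set is the denominator of the primary percentage and the population for the Cox models, the Kaplan–Meier curves and the onset-time analysis. State also whether the sample taken at first-line progression counts towards the primary endpoint, so that the entry condition and the endpoint cover a consistent period.

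The main correction is one phrase in the protocol, and in the statistical analysis plan if it repeats the wording. It needs no additional patients, samples or assays. It restores the stated precision at n = 110 and makes the section consistent with its own comparisons. It should be made before the mutation results are analysed, so that the denominator is not settled with the data in view.

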### Ethical considerations

The final protocol of this study was approved by the ethics committee of the National Health Research Institutes, with reference number EC1060904. Official approval has also been obtained from the ethics committee of Kaohsiung Medical University Hospital (reference number: KMUHIRB-GII-20170027), Taipei Veterans General Hospital (reference number: 2017–12-003A), Cathay General Hospital (reference number: CGH-P107013), and National Cheng Kung University Hospital (reference number: A-BR-106-045). The study has been registered on the ClinicalTrial.gov website, with identification number NCT03401957. The trial will be performed in accordance with the 7th version of the World Medical Association’s Declaration of Helsinki, the International Council for Harmonization’s E6 (R2) Guideline for Good Clinical Practice, and regulatory laws in Taiwan. Prior to participation in this study, written informed consent will be obtained from each patient.

